**Fig. 1 Fig1:**
[figure not shown]
Dose-finding scheme in the MecMeth/NOA-24 trial

In phase II, the MFA dose determined in phase I will be applied. The potential participants will be screened. If they fit the inclusion criteria and give informed consent, there will be a 1:1 randomization. In the treatment arm, participants will receive standard TMZ + MFA (224 days at maximum). In the control arm, they will receive standard TMZ as described above.

### Criteria for discontinuing or modifying allocated interventions {11b}

For the individual patient, MFA therapy within the trial will be stopped if one of the following criteria applies:
Unequivocal MRI signs of disease progression according to RANO criteriaCTCAE5 grade 4 myelotoxicity/hematotoxicity for > 14 days in courses 1 and 2 related to MFA treatmentCTCAE5 grade 3+ for any other organ toxicity related to MFA treatment except for asymptomatic laboratory changes CTCAE5 grade 3Definitive termination of standard TMZ therapyAny event that leads to a delay in TMZ dosing lasting > 8 weeks from the beginning of the previous course of TMZAny adverse event, laboratory abnormality, or intercurrent illness which, in the judgment of the investigator, presents a substantial clinical risk to the subject with continued MFA applicationPregnancyLack of compliance of the subject (e.g., taking prohibited medication)Significant protocol violationsEvents probably related to the tumor resection/perioperative treatment or the underlying disease will not lead to discontinuation

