### Trial design {8}

The study consists of a single-arm phase I part and a randomized, parallel-group, and unblinded phase II part.

In phase I, patients with the first relapse of MGMT-methylated glioblastoma are screened for the trial. After inclusion, patients are pretreated with MFA in addition to standard TMZ and tumor resection will be performed 7–10 days after initiation of therapy. MFA tissue level measurements and translational analyses are performed on the tumor material obtained from resection. Each patient is particularly screened for dose-limiting toxicities (DLTs) during the first 8 weeks of his/her MFA treatment. Patients are recruited in two cohorts of three to six patients. Dose adaptation in between cohorts depends on the occurrence of DLTs as described below.

All patients of phase I are followed for toxicity and efficacy until the end of phase II.

In phase II, patients with the first relapse of MGMT-methylated glioblastoma are screened for the trial. After inclusion, patients are randomized (1:1) into two parallel groups, the experimental or the standard treatment arm. The experimental treatment is defined as treatment with MFA (dose determined in phase I) in addition to standard TMZ. The standard treatment arm is defined as monotherapy with TMZ (150–200 mg/m^2^ body surface). If tumor resection for the relapsed tumor is clinically indicated, the local treating neurosurgeon can decide whether the resection can be safely postponed until day 7–10 after initiation of therapy (optional, not a prerequisite for study participation in phase II) and tumor material for determination of MFA levels can be obtained.

MFA is taken at the dose determined in phase I. Daily MFA treatment is continued for 8 4-week courses (i.e., 224 days), until tumor progression, until the occurrence of a DLT attributable to MFA, or until definitive discontinuation of standard TMZ, whatever comes first. In case MFA therapy is terminated, standard TMZ therapy can be continued at the discretion of the treating physician.

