### Intervention description {11a}

In phase I, there is one treatment arm and a dose-finding algorithm will be performed as described in the following. The participants will receive standard TMZ therapy for eight cycles (TMZ application orally on day 1–5 in a 28-day cycle, dose 150–200 mg/m^2^ body surface). In addition to that, the first three patients will receive 2 × 100 mg/day MFA daily (see also Fig. 1 dose-finding scheme). If no DLT occurs, the next three patients will be treated with 2 × 200 mg/day. Again, if no DLT occurs, this dose will be used for phase II. In both steps, if 1/3 patients develop a DLT, another three patients will be included. If there is a DLT in 1/6 patients, the dose will be elevated or the 2 × 200 mg/day dose will be used for phase II. If > 1 DLTs occur, the dose will be reduced in a next step to 2 × 50 mg/day and the same algorithm will be applied. If there are > 1 DLTs in 6 patients and the lowest dose of 2 × 50 mg/day, phase II will not be initialized. DLT is determined in the first 2 courses of MFA (within 8 weeks/56 (±3) days after first study treatment administration) in subjects with a compliance rate of 90% (i.e., 50 days of treatment) and no overdose. If judged to be related to the administration of MFA, the following toxicities will be considered a DLT: grade ≥ 4 hematotoxicity for > 14 days in courses 1 and 2; grade ≥ 3 for any other organ toxicity.

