### Outcomes {12}

In phase I, the primary outcome to be evaluated will be the incidence of DLTs during the first 8 weeks of MFA treatment. DLT for each dose level is defined as any CTCAE5 grade 3/4 organ toxicity or grade 4 hematotoxicity > 2 weeks during the first 8 weeks of MFA treatment; events probably related to the tumor resection and/or perioperative treatment or to the underlying disease are not regarded as DLT. Secondary outcomes in phase I are progression-free survival (PFS) as measured from the inclusion into the trial until diagnosis of progressive disease determined by MRI (according to “response assessment for neurooncology” (RANO) criteria) in the local center, PFS according to post hoc central reference neuroradiological assessment, overall survival (OS) as measured from the day of inclusion into the trial, assessment of safety beyond 8-week MFA treatment, and Karnofsky Performance Score (KPS), Quality of life (QoL), and Mini-Mental State Examination (MMSE) throughout the trial.

In phase II, the primary outcome to be evaluated will be PFS (randomization until the diagnosis of progressive disease according to RANO criteria). Secondary outcomes will be OS (randomization until death), continuous monitoring of AE/severe adverse events (SAE)/suspected unexpected serious adverse reactions (SUSARs), and quality of life throughout the trial (measured by KPS, QoLs, and MMSE). Survival analyses also include patients from phase I who received MFA at the same dose as applied in phase II.

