Briefly, patients start therapy within 7 days after inclusion/baseline visit. If according to the local treating neurosurgeon and the local neurooncological tumor board, re-resection of the tumor is clinically indicated and can be safely deferred until day 7–10 after initiation of MFA/TMZ therapy, tumor resection is performed 7–10 days after initiation of therapy. This is mandatory in phase I and optional in phase II. Resected tumor tissue is used for translational analyses of intratumoral MFA/MFA metabolite levels and detection of cellular and molecular effects of MFA. Also, blood analyses are performed for the determination of MFA blood levels 2 h after the first intake of MFA on day 1 and at 5 timepoints on the day of resection. During therapy, further visits are scheduled every 4 weeks prior to the start of a new TMZ cycle. These visits include clinical and standard laboratory examinations, documentation of co-medication documentation of (S)AE, KPS, and, every 8 weeks, contrast-enhanced MRI and QoL evaluation. In phase I, DLT evaluation is added at the visits prior to cycle 2 (day 28 ± 3) and cycle 3 (day 56 ± 3). MFA/TMZ treatment ends after 8 4-week cycles, at progression, or if MFA or at the timepoint when MFA or TMZ treatment has to be prematurely discontinued for whatever reason, e.g., intolerable toxicity, whatever comes first. After the end of the study therapy, patients are followed with clinical examination, contrast-enhanced MRI, and documentation of KPS, QoL, and further tumor therapy every 8 weeks. End of study and of follow-up in the entire trial will be reached when both of the following requirements are fulfilled: (1) at least 6 months after randomization of the last patient in phase II and (2) at least 3 days after definite termination of MFA intake in the last patient receiving MFA therapy (i.e., all patients have concluded study-related MFA intake for more than 3 days).

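### The only hematologic stop for meclofenamate with a stated grade and duration ends after course 2, although treatment runs for up to eight courses

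*Protocol article*

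**What the plan says.** Section {11b} of the protocol article lists the events at which MFA is stopped in an individual patient. The hematologic item reads "grade 4 myelotoxicity/hematotoxicity for > 14 days in courses 1 and 2 related to MFA" treatment. The next item stops MFA for MFA-related grade 3 or higher toxicity of any other organ, except asymptomatic grade 3 laboratory changes, and has no course limit.

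Section {8} sets the planned length and a further stop: "Daily MFA treatment is continued for 8 4-week courses (i.e., 224 days), until tumor progression, until the occurrence of a DLT attributable to MFA". Section {11a} repeats the length for the phase II experimental arm: "participants will receive standard TMZ + MFA (224 days at maximum").

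The DLT definition uses the same window as the stopping item. Section {11a} states that "DLT is determined in the first 2 courses of MFA", and its hematologic component is grade 4 or higher "hematotoxicity for > 14 days in courses 1 and 2". Section {12} defines a DLT as "any CTCAE5 grade 3/4 organ toxicity or grade 4 hematotoxicity > 2 weeks during the first 8 weeks of MFA treatment".

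The other stops that could reach a late blood toxicity are in {11b} (definitive end of TMZ, a TMZ delay of more than 8 weeks from the start of the previous course, and an investigator's judgment of substantial clinical risk) and in {13}, which ends treatment when MFA or TMZ "has to be prematurely discontinued for whatever reason, e.g., intolerable toxicity, whatever comes first".

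**The concern.** An eight-week window suits a DLT definition, because dose finding needs a fixed observation period. A stopping rule has a different purpose: it protects the individual patient for as long as the drug is given. Here the same window appears in a rule that governs up to eight courses in both phases, and no reason is given.

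Suppose a grade 4 cytopenia has lasted more than 14 days and been attributed to MFA. In course 2 the protocol requires MFA to stop. In course 3 or later it sets no threshold, and an express limit invites the reading that no stop is required. Sites may then handle the same event differently.

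The protocol itself recognises a bleeding hazard under MFA. It restricts antiplatelet and anticoagulant therapy ({10}, {11d}) and recommends proton pump inhibitor prophylaxis ({11d}). Prolonged grade 4 thrombocytopenia would add to that hazard in any course.

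**Working it through.** **Inputs.** Eight courses of 4 weeks, 224 days ({8}). Hematologic stop limited to courses 1 and 2 ({11b}). TMZ cycle of 28 days ({11a}). TMZ-delay stop at more than 8 weeks from the start of the previous course ({11b}). Visit spacing ({13}): "During therapy, further visits are scheduled every 4 weeks prior to the start of a new TMZ cycle".

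**Span of the gap.**
- Planned length: 8 × 28 = 224 days, which reproduces the article's figure.
- Covered by the hematologic threshold: 2 × 28 = 56 days; 56 / 224 = 25%.
- Not covered: 224 − 56 = 168 days; 168 / 224 = 75%, or 6 of 8 courses.

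**Does another rule supply the threshold in courses 3 to 8?**

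| Rule | Reaches courses 3–8? | Sets a hematologic grade or duration? |
|---|---|---|
| Grade 3+ toxicity of other organs ({11b}) | Yes | No; the hematologic item comes first and this one covers other organs only |
| DLT attributable to MFA ({8}) | No; DLTs are confined to the first two courses or 8 weeks ({11a}, {12}) | Only within that window |
| TMZ delay over 8 weeks ({11b}) | Yes | No; acts through TMZ timing |
| Definitive end of TMZ ({11b}) | Yes | No |
| Investigator judges substantial risk ({11b}) | Yes | No |
| Discontinuation for intolerable toxicity ({13}) | Yes | No |

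**How far the TMZ-delay rule reaches.** The next TMZ course is due 28 days after the previous one began, and the rule acts after 56 days. The next course can therefore be up to 56 − 28 = 28 days late without triggering it. As an illustration (these days are assumed), a grade 4 cytopenia from day 20 to day 40 lasts about 20 days and so exceeds 14. TMZ could restart between day 41 and day 56, and the delay rule would not act. MFA is taken daily and could continue throughout.

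**Comparison within the list.** In course 6, a symptomatic grade 3 toxicity of another organ attributed to MFA must stop MFA. A grade 4 marrow toxicity of three weeks attributed to MFA need not.

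**Detecting the event.** Scheduled visits are 28 days apart, so a period of more than 14 days can fall wholly between two of them. Confirming the duration may need interim counts. This already applies in courses 1 and 2.

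The article gives no rate for MFA-related grade 4 hematotoxicity lasting more than 14 days, so no patient count can be calculated.

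**The case against.** The strongest reply is that late courses are already covered. The judgment item expressly includes laboratory abnormalities, so it reaches any cytopenia. The TMZ-linked stops have no course limit. For the gap to matter, an investigator must attribute a prolonged grade 4 cytopenia to MFA, see no substantial risk in continuing it, and neither end TMZ nor delay it beyond the limit. Attribution is a judgment in every course ({22}), so the change removes only the second of two judgments. This stands as a limit on the size of the problem. It does not supply a threshold, and an event of roughly 15 to 28 days could escape the TMZ-delay rule.

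A second reply is that the limit may be deliberate: a fixed rule early, then individual judgment once TMZ exposure has accumulated and attribution is harder. That is possible, but the article does not say so, and it does not explain why MFA-related toxicity of other organs keeps a fixed threshold in every course.

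A third is that an article condenses the full protocol, where course-by-course hematologic rules may stand. That could excuse silence about later courses. It does not explain an express restriction in the published rule.

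Oversight also gives partial cover. The data and safety monitoring board reviews safety data ({21a}) and the sponsor makes a second causality assessment of serious adverse events ({22}). Neither sets a grade or duration at which a patient's MFA stops.

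**Conclusion.** The concern holds. The only hematologic MFA stop with a grade and duration applies to 56 of up to 224 treatment days, and no other rule in the article extends it to the remaining 168. The 75% describes the span of the gap and does not measure risk. The number of patients affected is unknown and probably small, given the other stops.

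The conclusion rests on two readings: that the restriction to courses 1 and 2 means what it says, and that the item on other organs leaves hematotoxicity out. Whether the window was intended cannot be settled from the article. This is a patient-safety point about the wording of a stopping rule. It does not change the intention-to-treat population, alpha, power or sample size. It should be corrected because the correction is cheap and removes an unexplained inconsistency.

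**What to change.** In section {11b}, delete the restriction to courses 1 and 2, so that MFA-related CTCAE5 grade 4 myelotoxicity or hematotoxicity lasting more than 14 days stops MFA in any course. Keep the eight-week window in the DLT definition in {11a} and {12}, so that dose finding is unchanged. If the window was intended, state the reason and give a separate threshold for courses 3 to 8.

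The cost is one phrase in the protocol. There may be a few more MFA stops in courses 3 to 8, and some patients will need interim blood counts to confirm the duration, of a kind the current rule already needs in courses 1 and 2.

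### An MFA-related asymptomatic grade 3 laboratory change in the first 8 weeks ends MFA under Trial design {8} with the DLT definitions, but is exempt from the stop rule in {11b}

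*Protocol article*

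**What the plan says.** Four sections of the protocol article bear on the same event.

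- **Intervention description {11a}** sets the dose-finding rule. It opens the DLT definition with "If judged to be related to the administration of MFA, the following toxicities will be considered a DLT" and then lists "grade ≥ 4 hematotoxicity for > 14 days in courses 1 and 2; grade ≥ 3 for any other organ toxicity".
- **Outcomes {12}** defines the phase I primary outcome as "any CTCAE5 grade 3/4 organ toxicity or grade 4 hematotoxicity > 2 weeks during the first 8 weeks of MFA treatment". Its only exclusion is that "events probably related to the tumor resection and/or perioperative treatment or to the underlying disease are not regarded as DLT".
- **Trial design {8}** lists the events that end daily MFA, the earliest one deciding. One of them is that MFA runs "until the occurrence of a DLT attributable to MFA".
- **Criteria for discontinuing {11b}** repeats the two toxicity criteria as stop rules for the individual patient. The non-haematological one, grade 3 or higher, reads "for any other organ toxicity related to MFA treatment except for asymptomatic laboratory changes", with the exemption limited to grade 3.

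The same list in {11b} also lets the investigator stop MFA for a laboratory abnormality judged to put the patient at material risk.

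**The concern.** The exemption in {11b} is needed only if an asymptomatic laboratory change would otherwise be an organ toxicity. On the document's own usage, then, such a change at grade 3 falls within "grade ≥ 3 for any other organ toxicity" in {11a} and "any CTCAE5 grade 3/4 organ toxicity" in {12}, and neither section takes it out again. It is therefore a DLT, and {8} ends MFA at a DLT attributable to MFA. {11b} says that the same finding does not meet the stop criterion.

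What is at stake first is the treatment of the individual patient: a site that meets this event cannot follow both sections. Second, {8} and {11b} read together suggest that the event is not a DLT. That casts doubt on a count which is the phase I primary outcome and which fixes the phase II dose from 3 to 6 patients per level.

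**Working it through.** **Step 1: one event, four sections.** Take an asymptomatic grade 3 ALAT or creatinine rise, judged related to MFA, in week 5.

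| Section | Question it answers | Result for this event |
|---|---|---|
| {11a} | Is it a DLT? | Yes: MFA-related, grade 3, non-haematological, no exemption |
| {12} | Is it a DLT? | Yes: not among the listed exclusions |
| {8} | Does MFA end? | Yes: it is a DLT attributable to MFA |
| {11b} | Does the toxicity criterion stop MFA? | No: expressly exempt |

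**Step 2: scope.**
- Only non-haematological values are affected. Haematological toxicity becomes a DLT only at grade 4 lasting more than 14 days.
- The event would be seen: the laboratory panel in the notes to Table 1 covers sodium, potassium, creatinine, ASAT, ALAT and bilirubin.
- DLTs are defined only for the first 8 weeks, so the conflict lies in that window.
- The two sections cannot be separated by time. The haematological criterion in {11b} is tied to courses 1 and 2, so {11b} is meant to operate during the DLT window. Its non-haematological criterion has no time limit.

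**Step 3: effect on the dose rule.** Under {11a}, 0 DLTs in 3 patients clears a level, 1 in 3 adds three patients, 1 in 6 clears, and more than 1 fails it. In a first cohort with no other DLT, one such event counted or not counted is the difference between clearing the level and adding three patients. Two such events fail the level.

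**Step 4: illustration.** The document gives no probability of passing a dose level, so there is no figure to reproduce. It also gives no rate for either kind of event; all rates below are assumptions. With q = 1 − p,

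P(level clears) = q³ + 3pq² × q³ = q³ + 3pq⁵

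If other DLTs (rate a) and laboratory changes (rate b) are independent, p = 1 − (1 − a)(1 − b).

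For a = 10%:
- not counted: p = 0.10; 0.729 + 3 × 0.10 × 0.590 = 0.91
- b = 5%: p = 1 − 0.90 × 0.95 = 0.145; result 0.82
- b = 10%: p = 1 − 0.90 × 0.90 = 0.19; 0.531 + 3 × 0.19 × 0.349 = 0.73
- b = 20%: p = 1 − 0.90 × 0.80 = 0.28; 0.373 + 3 × 0.28 × 0.193 = 0.54

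Range over the assumed rates:

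| Other DLTs | Not counted | Counted, 5% | Counted, 10% | Counted, 20% |
|---|---|---|---|---|
| 5% | 0.97 | 0.91 | 0.82 | 0.62 |
| 10% | 0.91 | 0.82 | 0.73 | 0.54 |
| 20% | 0.71 | 0.62 | 0.54 | 0.38 |

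**The case against.** The best defence is that the two rules have different jobs. {11a} and {12} decide what counts for dose-finding; {11b} decides when an individual stops. A toxicity may count against a dose without ending that patient's treatment. This would dispose of the point if {8} did not make a DLT attributable to MFA a reason to end MFA. Because {8} ties the two together, the difference in scope does not resolve the conflict over stopping.

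The same argument does limit how far the point reaches:

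- **Dose decision.** A reader might infer that the dose decision depends on which section is read. The text does not go that far. {11a} and {12} agree that the event counts, and {11b} neither defines a DLT nor mentions dose steps. In addition, the DSMB determines whether a DLT has occurred ({20c}) and reviews DLT data after each dose step ({21a}), so classification is not left to each site. The doubt arises only by reading {8} and {11b} together.
- **Phase II exposure.** A reader might also infer that MFA exposure in phase II will vary from site to site. The stop sentence in {8} does follow the phase II description, but the DLT visit is held only in phase I, and no DLT assessment is described for phase II. There the conflict rests on the word DLT in {8} alone.
- **Not an absolute exemption.** Investigator judgement under {11b} can still stop MFA. That is discretion, however, and does not reconcile an automatic stop with an exemption.
- **Rates.** Eligibility limits baseline liver and creatinine values and excludes liver toxicity above grade 1 in first-line therapy, so the event may be rare. At low rates the shift in clearance is small.

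Finally, this is a condensed article and the dose-finding figure is not shown. The full protocol may carry a qualifier that was lost. The article nonetheless states all four rules, and they disagree.

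**Conclusion.** The article contradicts itself on one defined event: an MFA-related, asymptomatic grade 3 non-haematological laboratory change in the first 8 weeks. {8} with {11a} and {12} ends MFA; {11b} exempts the event. This follows from the wording and needs no assumption about rates. It is direct in the DLT window and clearest in phase I.

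The consequence for the phase I dose is secondary and inferred. It is material only because the cohorts are so small that one reclassified event can replace escalation by expansion. The clearance probabilities show sensitivity under assumed, independent rates at a single level. They are not estimates of what will happen in this trial and should not be cited as such.

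**What to change.** Reconcile {8}, {11a}, {11b} and {12} so that the document answers two questions without ambiguity for asymptomatic grade 3 non-haematological laboratory changes related to MFA: do they count as a DLT, and do they stop MFA? If the two answers are meant to differ, all four sections must be worded so that they can be followed together. Which answers are right is a clinical decision for the sponsor and is not judged here.

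Optionally, list such events separately in the phase I interim report to the DSMB, so that the board can see whether the dose recommendation depends on them.

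The cost is one statement carried through four sections and, if wanted, one line in the interim table. No extra patients, visits or tests are needed. If the full protocol already settles the matter, only the article needs correcting. If it does not, a change that can affect participants' safety would go through the substantial-amendment route in {25}.
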